## 1. Study Background

### 1.1 Burden and recurrence risk of acute mild ischemic stroke

Ischemic stroke is associated with higher rates of morbidity, recurrence, disability, and mortality, especially in Asian populations. Among them, non-disabling ischemic cerebrovascular events are the most common (accounting for more than 50% of all cerebrovascular diseases) and the recurrence rate is as high as 10-20%. Previous studies have found that early onset, severe artery stenosis and multiple infarctions are high risk factors for stroke recurrence in these patients.

**(1) The early stage of onset:** In the cohort studies, stroke recurrence in patients with ischemic stroke was mostly within 30 days after onset. In patients with TIA or minor stroke of large-artery atherosclerosis origin, the risk of recurrence is high within 7 days after onset.

**(2) Severe artery stenosis:** Early cohort studies showed that the risk of stroke recurrence caused by large-artery atherosclerotic stenosis was greater than that caused by other etiological types. The TIA.org study published in 2016 showed that the recurrent stroke risk in 90 days and 1 year of TIA and minor stroke caused by large-artery stenosis is the highest. The results from the imaging subgroup of the Clopidogrel in High-Risk Patients with Acute Nondisabling Cerebrovascular Events (CHANCE) suggested that the risk of stroke recurrence in patients with TIA and minor stroke with intracranial arterial stenosis in 90 days was significantly higher than those without intracranial stenosis. The results of the WASID study indicated that the risk of stroke recurrence in patients with symptomatic intracranial artery stenosis (stenosis rate  $\geq 70\%$ ) is higher than those with a stenosis rate of 50-70%. Besides, the Chinese Intracranial Atherosclerosis Study (CICAS) reported that the proportion of patients with extracranial or intracranial arterial stenosis occlusion was as high as 46.6%. Of these cases, 37.5% had only intracranial arterial stenosis, 4.9% had only extracranial arterial stenosis, and 9.1% had intracranial and extracranial arterial stenosis. Patients with large-artery atherosclerotic stenosis had higher risk of recurrence and poorer prognosis. During 12-month follow-up, it was found that the risk of recurrent stroke increased with the severity of stenosis.

**(3) Multiple infarctions:** A large number of studies showed that the risk of stroke recurrence is high in ischemic stroke combined with acute multiple infarctions. Results of the TIA.org study and the CHANCE subgroup analysis indicated that multiple infarctions was an important imaging marker for the risk of stroke recurrence in TIA and minor stroke at 90 days. Results of studies on large-artery stenosis showed that patients with acute multiple infarctions from artery-to-artery embolism had a high risk of recurrent stroke. Therefore, the recurrence risk estimator at 90 days (RRE-90) identified multiple infarctions as an important imaging marker for risk assessment of stroke recurrence.

### 1.2 Current status of drug therapy for acute mild ischemic stroke

Despite the high incidence and recurrence of stroke, effective therapies are extremely limited for ischemic cerebrovascular disease. The medication of ischemic cerebrovascular disease mainly relies on thrombolytic therapy in the super acute stage, antithrombotic therapy in the acute stage and rehabilitation treatment. However, most patients with ischemic stroke are not eligible for thrombolytic therapy because

of its narrow "time window". Therefore, effective drug therapy is still needed to further reduce the risk of stroke recurrence in acute ischemic stroke. Existing evidence-based medicine includes:

### **1.2.1 Antiplatelet therapy**

#### **1.2.1.1 Dual antiplatelet therapy(DAPT) for patients with ischemic stroke within 24 hours of onset.**

The antiplatelet drugs recommended by 2014 AHA/ASA Guidelines for the Prevention of Stroke in Patients with Stroke and Transient Ischemic Attack include aspirin, clopidogrel, compound preparation with aspirin and dipyridamole, and ticlopidine.  Cilostazol is recommended as secondary prevention therapy for non-cardiogenic ischemic stroke in Chinese Guidelines for the Prevention of Stroke in Patients with Stroke and Transient Ischemic Attack.

The CHANCE study enrolled 5170 patients with acute mild ischemic stroke (NIHSS score  $\leq 3$ ) or high-risk TIA who were randomized and received antiplatelet therapy within 24 hours after symptom onset and found that the combined clopidogrel and aspirin continued for 21 days significantly decreased the incidence of stroke within 90 days, compared with aspirin monotherapy. (8.2% vs. 11.7%; HR 0.68; 95% CI, 0.57 to 0.81;  $P < 0.001$ ). 

#### **1.2.1.2 Patients with ischemic stroke within 3 days of onset may also benefit from DAPT**

A meta-analysis of 14 studies, including the CHANCE study, involving a total of 9,012 patients with ischemic stroke compared the efficacy and safety of dual antiplatelet therapy versus mono-antiplatelet therapy within 3 days of onset. The results suggested that dual antiplatelet therapy significantly reduced the risk of stroke recurrence (RR, 0.69; 95%CI, 0.60-0.80;  $P < 0.001$ ) and composite outcomes of stroke, TIA, acute coronary syndrome, and all-cause death (RR, 0.71; 95%CI 0.63-0.81;  $P < 0.001$ ) and there was no significant increase in the risk of major bleeding.  Our previous meta-analysis also found similar results.

The COMPRESS study enrolled patients with large-artery atherosclerotic stroke within 2 days of onset. The primary outcome was the presence of new ischemic lesion (both symptomatic and asymptomatic) on MRI at the 30th day. The results showed that, compared with aspirin alone, aspirin combined with clopidogrel did not reduce the new ischemic lesion on MRI at 30th day and did not increase the risk of bleeding.  However, some limitations of the study restrict the evaluation of efficacy, such as a small sample size and the lack of loading dose for clopidogrel at the early stage of administration, which may reduce the efficacy of the DAPT greatly.

#### **1.2.1.3 Patients with atherosclerosis or multiple infarctions might benefit most from DAPT**

The CARRESS study enrolled 230 SICAS patients with TIA and ischemic stroke. 107 patients with micro-embolism were randomized, and 51 patients were given clopidogrel and aspirin for 7 days and 56 patients were given aspirin alone for 7 days.  The results showed that DAPT significantly reduced the number of micro-embolism monitored by TCD compared to aspirin, without increased risk of intracranial hemorrhage. The CLAIR study enrolled 98 patients with TIA and ischemic stroke (NIHSS score was less than 8, symptomatic large-artery atherosclerotic stenosis with microembolism within 7 days of onset), and the results showed that the combination of clopidogrel and aspirin for 7 days significantly reduced the microembolism compared with aspirin, without increase in the risk of intracranial hemorrhage.  The

subsequent subgroup analysis of intracranial arterial stenosis found similar results. The above two studies based on subclinical outcomes showed that DAPT is a potential treatment of SICAS and short-term treatment did not increase the risk of bleeding.

For patients with TIA or minor ischemic stroke with intracranial arterial stenosis, subgroup analysis of the CHANCE study showed that the HR of stroke was 0.79 (0.47-1.32) in the group of aspirin and clopidogrel treatment, and 1.12 (0.56 -2.25) in the group of aspirin treatment in patients with intracranial atherosclerosis in 90 days. The P-value of interaction analysis was 0.522, which suggested that DAPT failed to effectively reduce the risk of stroke recurrence at 90 days in high risk patients with non-disabling cerebrovascular events of intracranial arterial stenosis. This subgroup had a small sample size, but the survival curve showed that intracranial arterial stenosis, rather than non-intracranial arterial stenosis, is likely to benefit more from DAPT compared with aspirin alone, which further provided important basis for clinical trials. The subgroup analysis also suggested that short-term DAPT did not increase the risk of bleeding. Another subgroup analysis of the CHANCE trial showed that multiple infarcts was an important imaging marker of stroke recurrence and patients with multiple cerebral infarctions and intracranial artery stenosis were at the highest risk of recurrence. Meanwhile, patients with multiple cerebral infarctions may benefit most from DAPT. The risks of stroke recurrence were 10.1% and 18.8% respectively in the groups of DAPT and aspirin alone (HR: 0.5; 95%CI: 0.3-0.96; P=0.04), which suggested that patients with multiple cerebral infarctions may be the most suitable target population of DAPT, especially patients with intracranial arterial atherosclerotic stenosis.

#### **1.2.1.4 New oral antiplatelet agents and anticoagulants remain to be explored**

The Acute Stroke or Transient Ischemic Attack Treated with Aspirin or Ticagrelor and Patient Outcomes (SOCRATES) trial published in 2016 enrolled minor stroke patients within 24 hours of onset and randomly assigned them to ticagrelor group and aspirin group. The patients were treated for 90 days and the primary outcomes were composite events (stroke, myocardial infarction, and death). The results showed that, for patients with high-risk TIA or minor ischemic stroke within 24 hours of onset, ticagrelor did not significantly reduce the 90-day combined risk of stroke, myocardial infarction and death compared with aspirin, and did not increase risk of any severe bleeding events. A subgroup analysis of the SOCRATES trial showed that compared with aspirin, ticagrelor could reduce the risk of stroke recurrence in TIA and minor ischemic stroke of large-artery stenosis. However, the results were not recommended by guideline because it was a subgroup of analysis.

### **1.2.2 Statin therapy**

#### **1.2.2.1 Secondary prevention study for statin**

Stroke Prevention with Aggressive Reductions in Cholesterol Levels (SPARCL) trial is the only study of the efficacy and safety of statin in patients with TIA or ischemic stroke so far. The study enrolled 4731 patients with non-cardiogenic (without atrial fibrillation or other cardiogenic embolism) stroke and (or) TIA, and they were randomized to the treatment of atorvastatin 80 mg/d or placebo, with an average follow-up of 4.9 years. The results showed that the baseline level of serum low-density lipoprotein cholesterol (LDL-C) was 3.3-3.5mmol/L, and after treatment, the level of LDL-C decreased to

1.9mmol/L in atorvastatin group, and 3.4 mmol/L in the placebo group. Intensive atorvastatin therapy significantly reduced the risk of recurrent stroke in patients with stroke and (or) TIA by 16% ( $P = 0.03$ ), and the risk of primary coronary events by 35% ( $P = 0.003$ ). This benefit was achieved on the basis of active antihypertensive and antiplatelet therapy.

The carotid stenosis subgroup of the SPARCL study revealed that patients with stroke and (or) TIA combined with carotid stenosis may benefit more from intensive atorvastatin therapy. In the subgroup analysis, intensive atorvastatin(80 mg/d) treatment significantly reduced the risk of recurrent stroke by 33% ( $P = 0.02$ ), reduced the risk of coronary events by 42% ( $P < 0.01$ ), and reduced the risk of carotid endarterectomy by 56% ( $P = 0.006$ ) in 1007 patients (21%) with stroke and (or) TIA combined with carotid stenosis. SPARCL subgroup analyses according to different types of stroke showed that intensive atorvastatin (80 mg/d) had a different degree of benefit for stroke patients with different subtypes, while patients with large-artery atherosclerotic stenosis may benefit more from statins.

### 1.2.2.2 Reversal effect of statins on carotid plaque

High resolution magnetic resonance imaging (HRMRI) has been widely used in monitoring the effect of statins on carotid atherosclerotic plaques. Early studies mainly focused on changes in atherosclerotic plaque burden (luminal area, wall area, vessel wall thickness, and normalized wall index) before and after medical therapy. Most studies found that statin significantly decreased the LDL-C level in serum, and improved the atherosclerotic plaque burden significantly over a certain period of time. Underhill et al reported that after the treatment of rosuvastatin for 2 years, the LDL-C level decreased significantly in atherosclerotic patients and the proportion of the lipid-rich necrotic core (LRNC) in the wall was decreased by 41.4% than that of baseline ( $P = 0.005$ ). Du et al found that LRNC decreased by an average of 7.3% ( $P = 0.044$ ) after the treatment of statin for 90 days, which suggested that statin therapy may stabilize atherosclerosis plaques in the first 90 days.

### 1.2.2.3 Study on statin therapy in acute stage

In addition to their LDL-lowering effects, statins have been found to possess various cytoprotective benefits, including protection of endothelial function, antioxidant properties, and anti-inflammatory effects. Preclinical studies have shown that administering statins immediately after a stroke can reduce the size of the infarct and improve neurological outcomes.

Currently, the studies of statin therapy for ischemic cerebrovascular disease were based on cohort studies and randomized controlled exploratory trials of small sample size. The prospective North Dublin Population Stroke Study published in 2011 enrolled 448 patients with ischemic stroke, and the results showed that initiating statin therapy within 72 h after stroke was significantly associated with the decrease of short-term and long-term mortality. A randomized controlled trial published in 2007 enrolled 89 ischemic stroke patients admitted within 24 hours of onset with chronic statin therapy. Patients were randomly assigned either to statin withdrawal for the first 3 days after admission or to immediately receive atorvastatin. The trial found that statin withdrawal was associated with increased risk of death or dependency at 90 days (OR, 4.66; 95% CI, 1.46-14.91). A recent Meta-analysis found that statin administration during hospitalization was associated with good functional outcomes (OR, 1.31;

95%, CI, 1.12-1.53;  $P = 0.001$ ). The Meta-analysis also revealed that the treatment of statins before stroke is related to better functional outcome (OR: 1.50; 95% CI: 1.29-1.75;  $P < 0.001$ ) and lower mortality (OR: 0.42; 95%; CI:0.21-0.82;  $P = 0.0108$ ). Similar results were found in patients with large-artery atherosclerosis and small-artery occlusion, but was not found in patients with cardiogenic embolic stroke.

39

A recent study enrolled 516 patients with acute ischemic stroke from large-artery atherosclerosis (TOAST subtype) and analyzed the impact of statin pretreatment on short-term outcomes. The study is a multicenter, prospective trial. The study concluded that statins pretreatment before stroke was independently associated with better functional outcomes (mRS score 0-1; OR: 2.44; 95%CI: 1.07-5.53), lower mortality (OR: 0.24; 95%CI: 0.08-0.75) and the rate of stroke recurrence (OR: 0.11; 95%CI: 0.22-0.46) within 1 month. Therefore, this study suggests that statins pretreatment has a positive effect on prevention of stroke.

However, several small-sample randomized controlled trials have found no improvements in stroke recurrence and functional outcomes from early statin initiation. The EUREKA study included 316 patients with ischemic stroke in Korea, who received rosuvastatin with a dose of 20mg daily or placebo within 48 hours of onset and found no significant difference in occurrence of new ischemic lesions on DWI at 5 or 14 days between the two groups. The STARS trial, a randomized controlled trial conducted in Spain, enrolled 104 patients with ischemic stroke with NIHSS score 4-22. The results suggested that simvastatin(40mg/d) started within 12 hours of onset did not improve the proportion of independent patients (mRS score $\leq$ 2) at 90 days compared with placebo. The ASSORT study conducted in Japan enrolled 257 patients with ischemic stroke (NIHSS score $\leq$ 20) and randomly assigned to receive statin initiated within 24 hours or 7-day delayed statin, the results of which showed no significant difference in risk of disability between the two therapies. This may be related to the small sample sizes of several studies, the variety of stroke causes enrolled, the severity of the disease, and the insufficient dosage of statins. **It is necessary to conduct large-scale randomized clinical trials for intensive statin therapy in the acute phase of large-artery atherosclerotic ischemic stroke.**

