|                | 
Day22±2 -Day 90: Clopidogrel 75mg/day+ aspirin placebo
 
Standard antiplatelet therapy :
 
Day 1: Aspirin 100-300mg/day + clopidogrel placebo
 
Day 2 - 90: Aspirin 100mg/day+ clopidogrel placebo
 
Immediate intensive statin therapy (atorvastatin 80mg/d) :
 
Day 1 -Day 21±2: Atorvastatin 80mg/day
 
Day22±2 -Day 90: Atorvastatin 40mg/day
 
Delayed intensive statin therapy (atorvastatin 40mg/d) :
 
Day 1 - Day3: Atorvastatin placebo
 
Day4 - Day21±2: Atorvastatin 40mg/day + Atorvastatin calcium placebo
 
Day22±2 -Day 90: Atorvastatin 40mg/day
                                                                                                                                                                                                                                                                                                                                                                                                                                                                                                                                                                                                                                                                                                                                                                                                                                                                                   |

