### Notes:

- Intensive antiplatelet therapy refers to dual antiplatelet therapy with aspirin and clopidogrel;
- Standard antiplatelet therapy refers to antiplatelet monotherapy with aspirin;
- Immediate intensive statin therapy (atorvastatin 80mg/d) refers to lipid-lowering therapy from the onset with atorvastatin at a dose of 80 mg daily and last for the first 21 days, followed by 40 mg daily for days 22-90;
- Delayed intensive statin therapy (atorvastatin 40mg/d) refers to lipid-lowering therapy with atorvastatin at a dose of 40 mg for days 4-90);
- Acute mild ischemic stroke or high-risk TIA patients attributed to extracranial or intracranial atherosclerosis: at least one of the following characteristics:
  - a) Mild ischemic stroke (NIHSS score 4–5) within 24 hours after onset and either of the following imaging characteristics:
    - 1) Acute single infarction with  $\geq 50\%$  stenosis of a major intracranial or extracranial artery that likely accounts for the infarction and clinical presentation.
    - 2) Acute multiple infarctions documented by head CT or MRI, attributed to large-artery atherosclerosis, including non-stenotic vulnerable plaques.
  - b) Mild ischemic stroke (NIHSS score  $\leq 5$ ) or high-risk TIA (ABCD score  $\geq 4$ ) within 24-72 hours after onset and meet any of the following imaging characteristics:
    - 1) TIA with  $\geq 50\%$  stenosis of a major intracranial or extracranial artery that likely accounts for the clinical presentation.
    - 2) Acute single infarction with  $\geq 50\%$  stenosis of a major intracranial or extracranial artery that likely accounts for the infarction and clinical presentation.
    - 3) Acute multiple infarctions documented by head CT or MRI, attributed to large-artery atherosclerosis, including non-stenotic vulnerable plaques.

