## 2.4 Subgroup analysis

**2.4.1** To evaluate the efficacy of intensive antiplatelet therapy versus standard antiplatelet therapy, immediate intensive statin therapy (atorvastatin 80mg/d) versus delayed intensive statin therapy (atorvastatin 40mg/d), and intensive antiplatelet combined with immediate intensive statin therapy (atorvastatin 80mg/d) versus standard antiplatelet combined with delayed intensive statin therapy (atorvastatin 40mg/d) in reversing intracranial atherosclerotic artery stenosis and stabilizing the atherosclerotic vulnerable plaque in the high resolution MRI subgroup.

**2.4.2** To evaluate the efficacy of intensive antiplatelet therapy versus standard antiplatelet therapy for 90 days on the incidence of the primary outcome in different subgroups:

- Subjects aged > 65 years vs. those aged ≤65 years.
- Female vs. male patients.

- Those with NIHSS score 4-5 vs. those with NIHSS score  $\leq 3$  at admission.
- Those randomized within 24 hours of onset vs. those randomized between 24 and 72 hours since onset.
- Those with ischemic stroke/TIA related to extracranial artery atherosclerosis vs. those related to intracranial artery atherosclerosis.
- Those with intracranial stenosis vs. those without intracranial stenosis.
- Those with extracranial stenosis vs. those without extracranial stenosis.
- Those with multiple infarctions vs. those with single infarction vs. those without infarction.
- Those with severe stenosis ( $\geq 70\%$ ) vs. those with moderate stenosis (50%-69%).
- Those with hypertension vs. those who are normotensive.
- Diabetic patients vs. nondiabetics.
- Those with dyslipidaemia vs. without dyslipidaemia.
- Those with atherogenic dyslipidaemia (HDL-C $<40$  mg/dL and TG $>200$  mg/dL) vs. without atherogenic dyslipidaemia.
- Those with statin therapy within 1 month before randomization vs. without statin therapy.

In addition, relevant subgroups will be examined for genetic variability and biomarker characteristics.

**2.4.3** To evaluate the efficacy of immediate intensive statin therapy (atorvastatin 80mg/d) versus delayed intensive statin therapy (atorvastatin 40mg/d) for 90 days on the incidence of the primary outcome in subgroups which is the same as those in 2.4.2.

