13. Dual antiplatelet therapy with aspirin and clopidogrel within 14 days before randomization (Patients who started aspirin plus clopidogrel without loading dose(300mg) of clopidogrel after onset are not excluded from the trial.).
14. High-intensity statin therapy within 14 days before randomization (e.g. atorvastatin  $\geq 40$ mg/d,

rosuvastatin  $\geq 20\text{mg/d}$ ).

15. History of intracranial hemorrhage (e.g. intracerebral or subarachnoid hemorrhage).
16. Gastrointestinal bleeding or major surgery within 90 days.
17. History of intracranial or extracranial angioplasty.
18. Planned long-term use of antiplatelet drugs or non-steroidal anti-inflammatory drugs except for study drugs.
19. Planned surgery or revascularization that may need to stop taking the study drugs within the next 90 days.
20. Anticipated life expectancy  $< 90$  days.
21. Currently participating in any other investigational drug or device study.
22. Unable to complete the follow-up (e.g. dementia, alcoholism, substance abuse, severe mental disease).

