##### 7.4.1 Concomitant medication contraindicated

- 1) Anti-platelet therapy: Ticagrelor, dipyridamole, cilostazol, ticlopidine, prasugrel, GPIIb/IIIa receptor antagonist, ozagrel etc.
- 2) All forms of anticoagulant drugs.
- 3) Thrombolytic therapy: rt-PA, urokinase and streptokinase etc. Patients who received intravenous or intra-arterial thrombolysis within 24 hours before randomization should not be included. If patients received intravenous or intra-arterial thrombolysis after randomization, the study antiplatelet agents must be discontinued for at least 24 hours before restart. While atorvastatin in the study is not affected.
- 4) Batroxobin, defibrase, snake venom preparation, lumbrukinase etc.
- 5) Non-steroidal anti-inflammatory drugs (NSAIDs, inhibitors of Cox1 and Cox2). Usage of NSAIDs (inhibitors of Cox1 and Cox2) within 7 days after randomization is violation to the protocol. If necessary, NSAIDs should be initiated after 24 hours after discontinuation of study drugs for less than 5 days, and should not be used within 8 days after randomization.
- 6) Potent inhibitor of CYP3A: Ketoconazole, nefazodone, ritonavir, saquinavir, atazanavir, nelfinavir, itraconazole, voriconazole, clarithromycin, telithromycin except for erythromycin and azithromycin;
- 7) Potent inducer of CYP3A: Rifampicin, dexamethasone, phenytoin, carbamazepine, oxcarbazepine, phenobarbitone;
- 8) Potent inhibitor of CYP2C19: Omeprazole, esomeprazole, fluvoxamine, fluoxetine, moclobemide, fluconazole, naphthyridine, ciprofloxacin, cimetidine, chloramphenicol;
- 9) Potent inhibitor of P-glycoprotein (P-gp): Verapamil, quinidine, cyclosporine;
- 10) Substrates of P-glycoprotein (P-gp): Digoxin. If necessary, If digoxin is absolutely necessary, reduce the digoxin dose as appropriate and monitor digoxin blood levels closely;
- 11) Other statins, drugs or food that affect the metabolism of statins: Rosuvastatin, simvastatin, pravastatin, pitavastatin, lovastatin, fiber acid derivative (fibrates), niacin or immunosuppressive regulating the lipid, oral contraceptive, hypocol.
- 12) Other relative drugs: evening primrose oil, curcumin, capsaicin staggerweed, ginkgo, garlic, the root of red-rooted salvia, cholestyramine.

13) Chinese patent drug : Chinese medicines with antiplatelet and antithrombotic effects in the instructions, including tablets and injections.

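### The overall statin effect averages delayed start in non-users with a three-day interruption in patients already on a lower-intensity statin, and the planned one-month subgroup does not separate the two

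*Supplement*

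**What the plan says.** All references are to protocol V4.0.

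- **Eligibility.** Section 5.2 item 14 excludes "High-intensity statin therapy within 14 days before randomization", with atorvastatin from 40 mg/d and rosuvastatin from 20 mg/d as examples. Lower-intensity use is not excluded. Section 2.4.2 lists the subgroup "Those with statin therapy within 1 month before randomization vs. without statin therapy", and 2.4.3 applies it to the statin comparison, so such patients are expected.
- **Regimen.** In the Summary and section 6.2, the delayed arm is "Day 1 - Day3: Atorvastatin placebo" for every patient, followed by 40 mg (section 2.1 Notes: "atorvastatin at a dose of 40 mg for days 4-90"). The immediate arm is "Day 1 -Day 21±2: Atorvastatin 80mg/day", then 40 mg.
- **Other statins.** Section 7.4.1 item 11 contraindicates "Other statins, drugs or food that affect the metabolism of statins: Rosuvastatin, simvastatin" and further named statins. Section 7.5.1 item 3 makes use of a contraindicated drug a reason to suspend study drug. Non-study atorvastatin is not named in item 11.
- **Background.** Section 1.2.2.3 describes a randomised trial in 89 chronic statin users admitted within 24 hours of onset. They were either withdrawn for the first three days or given atorvastatin at once. The reported result is "statin withdrawal was associated with increased risk of death or dependency at 90 days (OR, 4.66; 95% CI, 1.46-14.91".
- **Analysis.** Section 16.3.2.2 plans one marginal Cox comparison for the statin factor, stratified only by the antiplatelet factor. Section 7.1 describes blocked 1:1:1:1 allocation and mentions no stratification by prior statin use.

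**The concern.** Objective 2 is framed as immediate versus delayed intensive statin therapy. For a patient not on a statin, the arms differ in starting now or on Day 4. For a patient on a lower-intensity statin at onset, they differ in continuing at a higher dose or being interrupted for three days. The marginal hazard ratio averages these two contrasts in proportions the plan does not state.

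If interruption does harm, part of an observed advantage for the immediate arm would reflect a worse control course in users and not a gain from starting early. The reader would need to know how much. The regimen also repeats, for an identifiable eligible group, something close to what the background reports as associated with worse outcome, and no section comments on this.

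**Working it through.** **1. What each arm means by prior use**

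| Statin at onset | Immediate arm, Days 1-3 | Delayed arm, Days 1-3 | Contrast |
|---|---|---|---|
| None | 80 mg | placebo | start now versus Day 4 |
| Low or moderate intensity | 80 mg | placebo, other statins contraindicated | escalate versus interrupt |

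On Days 4-21 both rows also carry a dose difference, 80 versus 40 mg.

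**2. What the one-month subgroup contains.** It holds (a) lower-intensity users at onset; (b) patients who stopped within the month but before onset, including high-intensity users who stopped more than 14 days before randomisation; and (c) patients who first took a lower-intensity statin between onset and randomisation. Only (a) is interrupted from established use. Group (c) is limited, because item 14 has no exception for high-intensity statins started after onset.

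**3. Reproducing the plan's power.** Section 16.1 Table 2 has 2896 per side, 9.30% versus 11.57%, two-sided 0.05, power 0.807. The pooled two-proportion formula is

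z = [√n·|p1−p2| − 1.96·√(2p̄q̄)] / √(p1q1+p2q2)

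= (53.81×0.0227 − 1.96×0.4324)/0.4321 ≈ 0.866, giving power 0.807. The plan's figure reproduces.

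**4. Size under assumptions.** The documents give neither the share of users, f, nor the effect of interruption on 90-day stroke, w. Both are assumed here. If early start has no effect and the immediate-arm risk is 9.30%, then

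delayed-arm risk = 0.0930 × (1 − f + f·w).

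Example, f = 0.20 and w = 2: 0.0930 × 1.20 = 0.1116, so the apparent risk ratio is 0.0930/0.1116 = 0.833. Each cell shows the apparent risk ratio and the chance of a significant result favouring the immediate arm (0.025 if there were no difference at all):

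| f | w = 1.25 | w = 1.5 | w = 2 |
|---|---|---|---|
| 10% | 0.976; 0.05 | 0.952; 0.09 | 0.909; 0.22 |
| 20% | 0.952; 0.09 | 0.909; 0.22 | 0.833; 0.65 |
| 30% | 0.930; 0.14 | 0.870; 0.43 | 0.769; 0.93 |

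Six of the nine cells are at about 22% or less. The chance exceeds one half only when risk doubles and at least 20% are users.

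If the planned effect is real, interruption would exaggerate it: 0.0930/(0.1157×1.025) = 0.784 at f = 10%, w = 1.25, and 0.0930/(0.1157×1.20) = 0.670 at f = 20%, w = 2.

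**5. Power of the separate groups** (9.30% versus 11.57%)

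| f | Not on a statin, per side | Power | Users, per side | Power |
|---|---|---|---|---|
| 10% | 2606 | 0.765 | 290 | 0.143 |
| 20% | 2317 | 0.715 | 579 | 0.243 |
| 30% | 2027 | 0.657 | 869 | 0.340 |

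**The case against.** Several points on the other side stand.

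- **The comparison is not biased.** A reader might infer that a positive statin result would be spurious. The documents do not support that. Objective 2 compares two assigned regimens, and randomisation protects that comparison in a mixed population. What is at issue is how the average is interpreted.
- **Harm is not established for this setting.** A reader might infer that the protocol imposes a known harm. The cited trial had 89 patients, a confidence interval from 1.46 to 14.91, and death or dependency as its endpoint, not stroke. It enrolled within 24 hours, whereas V4.0 admits within 24 hours only strokes with NIHSS 4-5 and all others at 24-72 hours. Section 1.2.2.3 calls this evidence exploratory and also lists neutral trials of early statin; section 1.3.2 says evidence on when to start is lacking.
- **Prior statin use is already a planned subgroup**, and section 16.3.2.2 provides a Cox model for subgroups. Section 16.3 leaves detail to an SAP to be completed before database lock. That SAP is not shown, so the absence of a stated interaction test is not itself a fault.
- **Moving the main claim to non-users would be costly.** Power would fall from 0.807 to about 0.66-0.77 over 10-30% users.

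Two things remain. The subgroup's definition is in the protocol, and it pools groups with different exposures. It also covers only the primary outcome, while mRS 2-6 is the planned outcome closest to the cited finding. And no passage reconciles the background with the regimen for users at onset.

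**Conclusion.** The point holds as one of interpretation and of unreconciled passages. The primary comparison of strategies is valid, but the overall statin effect mixes two contrasts and the one-month subgroup cannot pull them apart. The size is unknown. It rests on an assumed user share and an assumed stroke multiplier, and at 10% users or fewer with a multiplier up to 1.5 the apparent risk ratio under no true effect stays at 0.95 or nearer to 1. The conclusion also assumes that non-study atorvastatin is not continued during Days 1-3, which the placebo phase implies but section 7.4.1 does not state. The remedy is a low-cost improvement and does not call for a change of primary analysis.

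**What to change.** 1. Reconcile section 1.2.2.3 with 5.2 item 14, 6.2 and 7.4.1 item 11 for patients taking a statin at onset. The clinical resolution is for the sponsor. Any review by arm should be confined to the DSMB, because review by trial leadership would compromise the blind.
2. In 2.4.2 and 2.4.3, replace the one-month subgroup with three levels: statin in use at onset; statin first started between onset and randomisation; neither. State that a statin stopped before onset counts as neither.
3. Pre-specify the interaction of statin assignment with this variable, for stroke and for mRS 2-6.
4. Keep the whole-population marginal comparison as primary. Add the analysis in patients not on a statin at onset as a supportive analysis for interpreting the timing claim.

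**Cost.** Wording in the protocol and SAP and one recoded variable from the medication history already collected (sections 10.2 and 10.9), provided that history records when the statin was started and stopped. The supportive analysis has power of about 0.77, 0.72 and 0.66 at an assumed 10%, 20% and 30% users, and the user subgroup is underpowered. The 80 versus 40 mg difference on Days 4-21 means that even non-users do not show the effect of timing alone.
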